### Analyses

Statistical analyses will be performed using SPSS version 21.0 (SPSS Inc., Chicago, IL, USA). All data will be analysed according to an intention-to-treat analysis. No interim analysis is planned. Glucose is not normally distributed, thus the between group difference in median glucose at 1 hour, 4 hours and 1 day postoperatively will be tested with the Kruskal-Wallis test and post-hoc testing using the Mann–Whitney *U* test. In case of missing glucose at one hour, the last glucose measured during surgery will be carried forward. Change in glucose will be analysed using repeated measurements ANOVA, with time as fixed effect and baseline glucose, time and the interaction between treatments as covariates. Furthermore a per-protocol analysis will be performed next to the intention-to-treat analysis. Finally, the between group differences of the secondary outcomes will be tested with the ANOVA, Kruskal-Wallis, student *t*, Mann–Whitney *U* and the Chi-square test, where appropriate.

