### Randomisation

If eligible, patients will be randomised into one of the three study arms. The randomisation will be 1:1:1 for each study arm, with stratification for insulin use. We will use block randomisation with random block sizes, ranging from 3 to 12. The randomisation will be performed with a computer based randomisation application (TENALEA Clinical Trial Data Management System). Patients and investigators are not blinded for the treatment allocation. All patients randomised will be included in the intention to treat analysis.

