### Laboratory measurements

HbA1c, potassium and fasting serum glucose will be determined 1 h prior to surgery. Fasting serum glucose and potassium will be determined 1 hour, 4 hours and on day 1 postoperatively. When the patient has an arterial catheter during the surgical procedure, arterial glucose will be measured.

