### Outcome measures

Our primary outcome measure is the difference in median serum glucose between the GIK, BR and LG arm 1 hour after surgery.

The secondary outcome measures are the difference in median serum glucose between the three study arms at 4 hours and 1 day postoperatively, the difference in the amount of insulin administered and difference in the occurrence of major, minor and diabetes related complications. the hourly measurements will be used to determine the perioperative area under the curve of the area outside the target range. In addition, the occurrence of mild or severe hypoglycaemia (glucose <4.0 mmol l^−1^ and <2.3 mmol l^−1^, respectively), hypokalaemia (<3.5 mmol l^−1^) or hyperkalaemia (>5.0 mmol l^−1^) is assessed. The difference in glucose variability, described as mean absolute glucose change (MAG), between study arms will be calculated [24]. The MAG is calculated by adding the absolute differences of the glucose values, divided by the time over which the measurements were taken.

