### Statistical analyses

#### Sample size calculation

A 1 mmol l^−1^ decrease in glucose resulted in a relevant decrease in postoperative complications **(**8.7 mmol l^−1^ ± 1.8 and 9.7 ± 2.4) in the RABBIT 2 surgery trial [10]. We used the following formula to calculate the sample size: . Assuming a power of 90%, a significance level of 5% and a drop-out rate of 10%, we will need 105 patients per treatment group to detect a relevant difference of 1 mmol l^−1^ between treatment groups. Thus in total, we will need 315 patients.

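### The primary Kruskal-Wallis and Mann-Whitney tests use neither the randomisation stratum (insulin use) nor HbA1c; they are valid, but give up precision that is free to recover

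*Protocol article*

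**What the plan says.** All references are to the Protocol article.

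- **Randomisation:** "The randomisation will be 1:1:1 for each study arm, with stratification for insulin use". Insulin use is the only stratification factor named.
- **Laboratory measurements:** "HbA1c, potassium and fasting serum glucose will be determined 1 h prior to surgery".
- **Outcome measures:** "Our primary outcome measure is the difference in median serum glucose between the GIK, BR and LG arm 1 hour after surgery".
- **Analyses, primary test:** non-normality is the reason given for rank methods, and the plan reads: "thus the between group difference in median glucose at 1 hour, 4 hours and 1 day postoperatively will be tested with the Kruskal-Wallis test". For pairs of arms the section then names "post-hoc testing using the Mann–Whitney *U* test". No stratum or covariate is attached to either test.
- **Analyses, the only adjusted model** (the quoted sentence ends by labelling its last terms covariates): "Change in glucose will be analysed using repeated measurements ANOVA, with time as fixed effect and baseline glucose, time and the interaction between treatments as". Insulin use and HbA1c do not appear in it, and it is not the test named for the primary outcome.
- **Sample size calculation:** the trial is sized "to detect a relevant difference of 1 mmol l^−1^ between treatment groups", using "8.7 mmol l^−1^ ± 1.8 and 9.7 ± 2.4" from an earlier trial.

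**The concern.** When randomisation is balanced within a factor that predicts the outcome, the arm means vary less than an unstratified test assumes. Variation between insulin users and non-users stays in the error term although the design has removed it from the comparison. The test then rejects slightly too seldom under the null and has less power than a stratified one.

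HbA1c is a different case. It is not a stratification factor, so omitting it does not conflict with the design. It is a missed opportunity: the value is collected anyway, and adjusting for it would narrow the comparison if it predicts 1-hour glucose.

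There is also a gap between test and target. The outcome is a difference, and the design target is 1 mmol/l. Kruskal-Wallis and Mann-Whitney compare rank distributions and do not by themselves return a difference in mmol/l that can be set against that target.

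What is at stake is efficiency and readability of the result, not the validity of the conclusion.

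**Working it through.** **Inputs from the article:** difference 1 mmol/l; SDs 1.8 and 2.4; power 90%; significance level 5%, read as two-sided; drop-out 10%; 105 patients per arm (all from Sample size calculation).

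**Assumed, because the article gives no value:** R², the share of variance in 1-hour glucose explained by insulin use and HbA1c together.

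**1. Reproduce the planned size.** Summed variance is 1.8² + 2.4² = 9.00.

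n = (1.96 + 1.2816)² × 9.00 / 1² = 94.57, so 95 per arm.

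For drop-out, 94.57/0.9 = 105.07, and 95 × 1.10 = 104.5. Strict rounding of 95/0.9 gives 106. The stated 105 is therefore reproduced by an unadjusted, two-sided comparison of two arms. A one-sided test needs only 78 before drop-out and does not fit. The planned size does not rely on adjustment.

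**2. Effect of adjustment on one pairwise comparison.** Evaluable per arm: 105 × 0.9 = 94.5.

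SE = √(9.00 × (1 − R²)/94.5); power = Φ(1/SE − 1.96); 95% CI half-width = 1.96 × SE.

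| Assumed R² | SE | Power | CI half-width (mmol/l) |
|---|---|---|---|
| 0 | 0.309 | 90.0% | 0.605 |
| 0.05 | 0.301 | 91.4% | 0.590 |
| 0.10 | 0.293 | 92.7% | 0.574 |
| 0.20 | 0.276 | 95.2% | 0.541 |
| 0.30 | 0.258 | 97.2% | 0.506 |

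This is a normal-theory formula for means, the kind that reproduces the article's sample size. It approximates the rank tests.

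**3. Check with the rank tests.** A simulation compared unadjusted Kruskal-Wallis with a rank ANCOVA (ranks regressed on insulin use, HbA1c and arm; 2-df arm test). Settings: 4,000 runs per scenario, 95 per arm, strata exactly balanced, 40% insulin users (assumed), normal outcomes with common SD √(9.00/2) = 2.121, and one arm lower by 1 mmol/l for power.

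| Assumed R², insulin use / HbA1c | Type I error, Kruskal-Wallis | Type I error, rank ANCOVA | Power, Kruskal-Wallis | Power, rank ANCOVA |
|---|---|---|---|---|
| 0 / 0 | 5.3% | 5.3% | 91.4% | 91.4% |
| 0.05 / 0.10 | 4.6% | 5.1% | 91.5% | 94.8% |
| 0.10 / 0.20 | 4.0% | 5.2% | 92.2% | 98.2% |

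Monte Carlo error on a 5% rate is √(0.05 × 0.95/4000), about 0.3 percentage points. The 4.6% is therefore within noise of 5%, while the 4.0% is clearly below it. With no prognostic value the two methods perform alike.

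**4. Which baseline value can be used.** Study procedures/interventions starts liraglutide at 17.00 on the day before surgery. Serum glucose taken 1 hour before surgery is thus already affected by treatment in that arm, and adjusting for it could remove part of the effect under study. HbA1c is drawn at the same time, but under a day of treatment cannot move it materially. Insulin use is fixed at randomisation.

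**The case against.** The strongest reply is that nothing here is wrong. The planned test holds its error rate, the sample size was set without adjustment, and an unadjusted rank test is an accepted choice. All of this stands. A reader might infer that ignoring the stratum invalidates the primary test; the simulated type I error, close to or below 5% within Monte Carlo error, shows that it does not.

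Three other stronger readings are tempting and are not supported.

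- **That the plan will report only p-values.** The article names no estimator or interval, but nowhere says that none will be given. It is a condensed account, and the full protocol and SAP, which may settle this, are not shown. A Hodges-Lehmann interval can also be obtained by inverting the Mann-Whitney test.
- **That HbA1c is a strong predictor.** The article does not show this. All arms are measured hourly and corrected by a shared insulin algorithm towards 6–8 mmol/l, which could weaken the link between baseline status and 1-hour glucose. The low end of the R² range is therefore realistic. The Discussion's remark on insulin-naïve and insulin-dependent patients may be a comparison of regimens and settles nothing either way.
- **That adjustment would make good a power shortfall from testing three pairs.** If 5% were split over three pairs, which the article does not propose, the critical value is 2.394. Power is then Φ(3.240 − 2.394) = 80.1% unadjusted and Φ(3.416 − 2.394) = 84.7% at R² = 0.10. That recovers 4.6 of the 9.9 points lost. If a significant Kruskal-Wallis result is required first, three arms need no split.

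It can also be said that a covariate-adjusted analysis is already planned. The repeated-measures model does use baseline glucose, but it is not the primary test, omits insulin use, and would inherit the problem in step 4 if baseline means a pre-operative reading.

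What remains is narrow. The published text fixes a primary test that leaves out the factor used to stratify. Because that is stated and not merely omitted, an SAP would have to change it.

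**Conclusion.** The point holds as one of efficiency and consistency with the design. The primary analysis ignores insulin use, the stratification factor, and does not use HbA1c, which is collected. The test remains valid.

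The gain in pairwise power is 1.4 percentage points at R² = 0.05, 2.7 at 0.10, 5.2 at 0.20 and 7.2 at 0.30, from a base of 90.0%. The confidence interval half-width falls from 0.605 to between 0.590 and 0.506 mmol/l over the same range. These figures rest on the article's SDs, 10% drop-out and an assumed R². If R² is near 0.05 the benefit is small; if it is zero, essentially nothing is lost by adjusting.

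**What to change.** Amend the primary analysis wording as follows.

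1. Account for insulin use in the primary test. Either use a stratified rank test of van Elteren type, extended to three arms, or a rank ANCOVA with insulin use and HbA1c. Name one in advance. Both keep the rank framework that the article chose for skewed glucose. ANCOVA on log glucose would instead estimate a ratio of geometric means, which does not read directly against 1 mmol/l.
2. Test the three arms globally first, then the pairwise contrasts by the same method.
3. Give each contrast a difference in mmol/l with a 95% confidence interval, for example stratified Hodges-Lehmann or adjusted median regression.
4. Keep unadjusted Kruskal-Wallis and Mann-Whitney as a sensitivity analysis.
5. Do not use pre-operative glucose as the adjustment covariate.

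The cost is wording. No extra patients or measurements are needed, since both variables are already recorded. Check that the chosen procedure can be run in the named software (SPSS 21.0). The trial is open-label and began in January 2014, so the change should be dated and final before any outcome is compared by arm.

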### Study procedures/interventions

In all patients, capillary glucose will be measured every 60 minutes, starting 30 min prior to surgery. The target range for plasma glucose for all study arms is 6–8 mmol l^−1^. An intravenous bolus of insulin will be administered according to treatment algorithm (Table 4). Capillary glucose will be measured using the Accu-Chek Inform (Roche diagnostics, Indianapolis, IL, USA).

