### Postoperatively

The assigned treatment will be continued up to 4 hours postoperatively. The patient will stay at the recovery room and will remain fasted. The treatment protocol will end 4 hours postoperatively. Hereafter, glucose will be monitored and treated according to the hospital protocol.

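### A missing 1-hour serum glucose is filled with an intra-operative reading 1–2 hours older, although a closer post-operative reading should usually be available

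*Protocol article*

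**What the plan says.** The Outcome measures section of the protocol article defines the endpoint: "Our primary outcome measure is the difference in median serum glucose between the GIK, BR and LG arm 1 hour after surgery". The Laboratory measurements section schedules the specimens. There is one serum sample 1 hour before surgery, and then "Fasting serum glucose and potassium will be determined 1 hour, 4 hours and on day 1 postoperatively". No routine serum sample during surgery is listed.

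Readings during surgery come from two other sources. The Study procedures/interventions section says: "In all patients, capillary glucose will be measured every 60 minutes, starting 30 min prior to surgery". The Laboratory measurements section adds: "When the patient has an arterial catheter during the surgical procedure, arterial glucose will be measured".

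The Analyses section gives the rule for a missing primary value: "In case of missing glucose at one hour, the last glucose measured during surgery will be carried forward". It names no other source for the replacement.

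On what happens after the operation, the Postoperatively section says: "The assigned treatment will be continued up to 4 hours postoperatively". Each arm's description includes glucose measurement every 60 minutes. The Outcome measures section uses the hourly values for an area outside the target range.

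**The concern.** The replacement differs from the endpoint in specimen, in time and in clinical situation. Carrying a value forward assumes that nothing changes afterwards, yet under this protocol an out-of-range reading leads to an action meant to change it. Table 4 gives an insulin bolus above 8 mmol/l in all arms, and glucose is given below 4 mmol/l. In the GIK arm only, a reading of 4–6 mmol/l also stops the infusion.

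The arms also differ in what is acting between late surgery and 1 hour afterwards: a glucose-insulin-potassium infusion, boluses alone, or liraglutide with boluses. The error in a carried value can therefore differ by arm and need not shrink the contrast, so the rule cannot be defended as conservative. The analysis also treats the filled values as if they had been observed.

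**Working it through.** **Step 1. Timing.** With readings every 60 minutes, the last one during surgery is 0–60 minutes old when surgery ends. The target is 60 minutes after the end. The carried value is therefore 60 + 0 = 60 to 60 + 60 = 120 minutes early. If the 60-minute series runs on after surgery, the nearest reading is at most 60/2 = 30 minutes from the target.

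**Step 2. Does the series run on?** No sentence says so outright. Three statements point that way: measurement is every 60 minutes with no stop time given, each arm's regimen includes it, and the assigned treatment lasts to 4 hours after surgery. This is a strong inference, not an explicit statement.

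**Step 3. A gap in the rule.** Readings start 30 minutes before surgery. On a strict 60-minute cycle the next falls about 30 minutes after the start. An operation shorter than that may have no intra-operative reading to carry.

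**Step 4. The plan's own scale.** The Sample size calculation section gives a difference of 1 mmol/l, SDs of 1.8 and 2.4, 90% power, 5% significance and 10% drop-out.

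- Pooled SD = √((1.8² + 2.4²)/2) = 2.12.
- Two-sided, this needs 95 per arm before drop-out.
- 95 × 1.1 = 104.5, so 105; 95/0.9 = 105.6, so 106.

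The stated 105 reproduces and is not in dispute. The standard error of a between-arm mean difference at 105 per arm is 2.12 × √(2/105) = 0.29 mmol/l.

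**Step 5. Possible bias (assumed inputs).** Let m be the share of 1-hour values filled in an arm, and d the average of carried value minus true 1-hour value. For arms A and B:

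bias in the mean difference = m_A·d_A − m_B·d_B

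- Equal m and equal d: the bias is 0. The bolus rule is common to all arms, so it creates no bias in the contrast by itself.
- Equal m, with d differing by 1–2 mmol/l: 0.05 × 1 = 0.05 up to 0.10 × 2 = 0.20 mmol/l, which is 5–20% of the target difference and 0.17–0.68 of the standard error.
- Equal d of 2 mmol/l, with 5% missing in one arm and 15% in the other: (0.15 − 0.05) × 2 = 0.20 mmol/l.

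**Step 6. Possible loss of power (assumed inputs).** Let f be the share of the 1 mmol/l effect already present in the carried value. The average effect becomes (1 − m) × 1 + m × f. The table shows power at 105 per arm with SD 2.12, using a comparison of two means. With nothing missing it is 92.7%.

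| m | carried, f = 0 | carried, f = 0.5 | complete cases |
|---|---|---|---|
| 5% | 90.1% | 91.5% | 91.5% |
| 10% | 86.7% | 90.1% | 90.0% |
| 20% | 78.0% | 86.7% | 86.3% |

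In this illustration, carrying forward is worse than dropping the patients when the carried value holds clearly less than half the effect. At one half the two are about level.

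Steps 5 and 6 work on means. The planned tests are Kruskal-Wallis and Mann-Whitney, so these figures are indicative only.

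**The case against.** The case for leaving the rule alone has real strength.

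- **Few values may be missing.** Patients remain in the recovery room, fasted and on protocol treatment, until 4 hours. The 1-hour sample is thus taken under supervision. No figure in the protocol supports 5–10%, and the 10% drop-out allowance is not a rate of missing 1-hour samples. This stands.
- **The shift is generous.** A between-arm difference of 1–2 mmol/l arising within 1–2 hours equals or doubles the whole target effect. This stands too, and is why the sizes are illustrations.
- **The rule has merits.** It is fixed in advance, gives one definite value, and helps to keep all randomised patients in the analysis. The nearest-reading rule keeps the first two merits, and its fallback keeps the third.
- **The closer reading may be missing too.** Whatever prevents the serum sample may also prevent a capillary reading. That is a reason for a fallback, not for going to an older reading first.

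A reader might infer that the rule demonstrably puts arm-dependent bias into the primary result. The documents do not show this. All arms share the glucose target and the bolus table, and neither the direction nor the size of any arm difference in shift can be derived. A reader might also infer that hourly post-operative readings certainly exist and are being ignored. As step 2 shows, that is inferred, not stated.

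**Conclusion.** The point holds as a modest weakness in a stated rule. The mismatch of specimen and the 1–2 hour gap follow from the protocol's own schedule, and any carried reading above 8 mmol/l is one that has just triggered a bolus. From this it follows that the primary comparison may be biased, in an unknown direction. It does not follow that it is biased, or that the trial's conclusion is at risk.

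The illustrative 0.05–0.20 mmol/l rests wholly on the assumed 5–10% missing and 1–2 mmol/l difference in shift. If almost no 1-hour values are missing, the effect is negligible. The reason to act is that a closer replacement should usually be available at almost no cost.

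**What to change.** Replace the sentence in the Analyses section with text along these lines:

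*If the 1-hour serum glucose is missing, the post-operative capillary or arterial reading nearest to 1 hour after the end of surgery, within 30 minutes either side, is used; of two equally near readings, the earlier is taken. If there is none, the value is estimated by a prespecified method from the patient's available glucose series, including the 4-hour serum value. The primary analysis is repeated with the last intra-operative reading carried forward, and with complete cases only.*

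The fallback method must be named. If it is multiple imputation, the plan must also say how Kruskal-Wallis and Mann-Whitney results are pooled across imputations. For a handful of patients, a single deterministic rule such as interpolation between the neighbouring readings may be enough. The plan should also state that hourly measurement continues to 4 hours, if that is the intention, and report the number of replaced values by arm.

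The cost is a few lines of text and a little programming, with no new data and no change in care. The downside is that a few capillary values stand in for serum, which the present rule already allows with older readings.

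### The repeated-measures model for change in glucose is loosely specified and, if run as classical repeated-measures ANOVA, would exclude patients missing a 4-hour or day-1 value, against the stated intention-to-treat set

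*Protocol article*

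**What the plan says.** The Laboratory measurements section sets the postoperative serum schedule: "Fasting serum glucose and potassium will be determined 1 hour, 4 hours and on day 1 postoperatively". The Analyses section tests glucose at each of these times separately, by Kruskal-Wallis with Mann-Whitney comparisons afterwards. It then adds a model across time: "Change in glucose will be analysed using repeated measurements ANOVA, with time as fixed effect", followed by "baseline glucose, time and the interaction between treatments as covariates". The software is fixed ("Statistical analyses will be performed using SPSS version 21.0"), but the SPSS procedure is not.

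Two statements define the analysis population. The Analyses section says "All data will be analysed according to an intention-to-treat analysis", and the Randomisation section says "All patients randomised will be included in the intention to treat analysis".

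There is one rule for missing values: "In case of missing glucose at one hour, the last glucose measured during surgery will be carried forward". Nothing is said about a missing value at 4 hours or on day 1. The sample size section allows for 10% drop-out.

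**The concern.** The article fixes a method, a population and a missing-value rule, and on the ordinary meaning of the method the three do not fit together. Classical repeated-measures ANOVA, which SPSS runs as GLM Repeated Measures, deletes cases listwise. A patient without a day-1 value would also lose valid 1-hour and 4-hour values, and the result would describe completers.

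The term list does not settle which model is meant. Time appears twice in different roles, the interaction is described as being between treatments rather than between treatment and time, and neither a treatment main effect nor a subject effect or covariance structure is named. A wording that allows both a completers-only and an all-available-data analysis leaves the choice open until the data are seen, in an open-label trial.

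Two things are at stake. Precision is lost whenever values are missing. Bias arises if missing a later sample is related to the patient's glucose, for example through complications, transfer or early discharge. This is the only named analysis of glucose over time and the only one that adjusts for baseline glucose.

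**Working it through.** **The plan's own figure.** Inputs from the sample size section: difference 1 mmol/l, SDs 1.8 and 2.4, power 90%, significance level 5% (taken as two-sided), drop-out 10%.

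- n per arm = (1.960 + 1.282)² × (1.8² + 2.4²) / 1² = 10.51 × 9.00 = 94.6, so 95.
- With drop-out: 95 × 1.10 = 104.5, so 105; or 95 / 0.90 = 105.6, so 106.

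The stated 105 per arm (315 in total) reproduces. The present point does not change it.

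**Patients kept under listwise deletion.** The protocol gives no missingness rate m per time point, so m is an assumption. If the 1-hour carry-forward is applied to this model, two times remain exposed (4 hours and day 1). With independent missingness the complete share is (1 − m)²:

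| m at each time | (1 − m)² | Patients of 315 | Per arm |
|---|---|---|---|
| 2% | 0.960 | 302 | 101 |
| 5% | 0.9025 | 284 | 95 |
| 10% | 0.81 | 255 | 85 |
| 15% | 0.7225 | 228 | 76 |

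If the same patients miss both times, the loss is only m: 315 × 0.95 = 299 or 315 × 0.90 = 284 (rounded) for 5% or 10%. If the carry-forward is not applied to this model, three times are exposed and the share is (1 − m)³: 270 patients at 5% and 230 at 10%. A likelihood-based mixed model keeps every patient with at least one observed postoperative value.

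**Bias if loss depends on glucose.** Simulation assumptions:

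- arm means 8.7 (SD 1.8) and 9.7 (SD 2.4) at all three times, so the true difference is 1.0 mmol/l;
- equal baseline means;
- one common correlation of 0.4 to 0.6 among baseline and the three postoperative values;
- loss before day 1 logistic in 1-hour glucose, set to 10% or 5% overall.

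The completers' mean over the three times was then compared between arms with adjustment for baseline, as the plan intends.

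| Log-odds of loss per mmol/l | Odds ratio per SD of 2.12 | Difference, 10% loss | Difference, 5% loss |
|---|---|---|---|
| 0 | 1 | 1.0 | 1.0 |
| 0.25 | exp(0.53) = 1.7 | 0.95–0.96 | 0.97–0.98 |
| 0.5 | exp(1.06) = 2.9 | about 0.90 | 0.94 |
| 1.0 | exp(2.12) = 8.3 | 0.81–0.82 | 0.88–0.89 |

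The SD of 2.12 is √((1.8² + 2.4²)/2). The bias reaches about 10% of the assumed effect only with 10% loss and log-odds of 0.5 or more, or with 5% loss and log-odds of 1.0.

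**The case against.** A reader might infer that the planned analysis simply is a completers-only analysis. The documents do not support that. No SPSS procedure is named. SPSS 21 also offers MIXED, which keeps patients with partial data, and the phrase about time as a fixed effect suits that procedure at least as well. In GLM Repeated Measures, time is the within-subject factor and cannot also be a covariate. The listwise consequence is therefore conditional on how the model is run. It is also too strong to say that any missing postoperative value removes a patient: the carry-forward covers the 1-hour value, if it is applied here.

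A reader might also infer that the trial's main results are at risk. They are not. The Outcome measures section does not list change in glucose. The primary outcome and the 4-hour and day-1 glucose outcomes are each tested at their own time, so a patient missing day 1 still counts in the primary test. For the same reason, a completers' difference at 1 hour is not a result the plan would report as its primary finding.

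The size is uncertain as well. The 10% drop-out is a sample-size allowance, not a missingness rate at 4 hours or day 1. Day-care surgery is excluded, and patients remain in the recovery room under study treatment until 4 hours, so loss at 4 hours may be small. The log-odds have no source in the documents, and 1.0 per mmol/l is a steep dependence.

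Finally, a condensed article may leave the procedure and covariance structure to a fuller document. That answers the absence of detail. It does not answer the contradictory term list, or the mismatch between the ordinary form of the named method and the stated population.

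**Conclusion.** The point holds in conditional form. The model sentence is ambiguous, and one ordinary way of carrying it out would restrict the analysis to patients complete at 4 hours and day 1, against the promise to include everyone randomised. It affects a supporting analysis and is worth correcting, but it does not threaten the primary comparison.

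The loss of patients would range from 5% or 10%, if the same patients miss both times, to about 10% or 19%, if values are missing independently at those rates. The bias is nil if missingness is unrelated to glucose, modest under moderate dependence, and near 0.2 of a 1.0 mmol/l effect only under 10% loss with the steepest dependence considered. These sizes rest on assumed missingness rates, correlations and dependence, none of which the protocol gives.

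**What to change.** Replace the repeated-measures sentence in the Analyses section with one along these lines: postoperative serum glucose at 1 hour, 4 hours and day 1 will be analysed with a linear mixed model for repeated measures (SPSS MIXED, REML), using all observed values from all randomised patients, with treatment, time, treatment-by-time and baseline glucose as fixed effects and an unstructured within-patient covariance; missing values are assumed missing at random given the observed data.

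Add that log-glucose will be used if residuals are skewed, since the same section says glucose is not normally distributed, and that arm contrasts will be reported at each time with 95% confidence intervals. Keep baseline glucose, because the plan already intends to adjust for it. The unstructured covariance suits the unequal spacing and the change to the hospital protocol after 4 hours. The model needs no carry-forward; that rule can stay with the 1-hour rank test.

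The cost is one or two sentences. Software, data and sample size stay the same.
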